## Abstract

**Background:**

Tobacco abuse is a frequent issue in general practitioners' (GPs') offices, with doctors playing a key role in promoting smoking cessation to their patients. However, not all smokers are ready and willing to give up smoking. Thus, a GP focusing on smoking cessation alone might waste the opportunity to improve his patient’s health by supporting a change in another harmful behaviour pattern. The aim of this study is to determine whether multi-thematic coaching will lead to higher overall health benefits without resulting in a reduced rate of successful smoking cessations, compared with a monothematic smoking cessation approach.

**Methods:**

The study is designed as a two-armed, double-blinded, cluster-randomised trial. GPs will be randomly assigned to the intervention or control group. In the intervention group, GPs will undergo training in patient-centred coaching, shared decision-making and motivational interviewing. The control group will be trained in a state-of-the-art smoking cessation algorithm.

GPs will approach adult cigarette-smoking patients and advise those included according to the GP’s group affiliation. The primary outcome is the between-group difference in the proportion of participants who achieve a beneficial change in at least one of seven different health-related behavioural dimensions, 12 months post baseline. Secondary outcomes include smoking cessation rates and the patients’ self-perceived smoking-related motivation, self-efficacy and planning behaviour. Additionally, covariates describing both GPs and patients will be collected before the start of the intervention, and process outcome measures in compliance with the RE-AIM (Reach Effectiveness Adoption Implementation Maintenance) framework will be recorded during the ongoing study.

**Discussion:**

Tobacco consumption is still highly prevalent in the general population and often goes hand in hand with other behaviour patterns with adverse health effects. This study will add to the literature regarding effective strategies available to GPs to address unhealthy behaviour among their smoking patients beyond mere smoking cessation counselling. The study will also establish a basis for decisions about further promotion and dissemination of the coaching under study.

**Trial registration:**

ISRCTN, ISRCTN38129107. Registered on 2 October 2017.

**Electronic supplementary material:**

The online version of this article (10.1186/s13063-018-3071-z) contains supplementary material, which is available to authorized users.

## Background

Tobacco use is a frequent issue in general practitioners' (GPs') offices, with doctors playing a key role in promoting smoking cessation to their smoking patients [1]. For this purpose, standardised brief interventions involving both counselling and supporting drug therapy have been established and evaluated for the primary care setting over the last years [2, 3].

However, not all smokers are ready and willing to give up smoking. Therefore, up-to-date stop-smoking programmes are based on the transtheoretical model of behaviour change [4] and thus take the patients’ readiness to stop smoking [3, 5] into account.

The patient-centred “Health Coaching” programme [6], developed by the Swiss College for Primary Care Medicine [7], is based on similar principles. Remarkably, this programme does not focus on smoking cessation or any other single health behaviour alone but includes several health-related behavioural dimensions in parallel. Particular emphasis is put on the patient-driven choice of which topic to address. The Health Coaching programme has proved its efficiency and practicability in a clinical trial carried out within the setting of primary care practitioners in eastern Switzerland [8].

Combining state-of-the-art smoking cessation counselling with the Health Coaching approach, exploring patients’ motivation for smoking cessation can be expanded into a more comprehensive exploration of their readiness to improve their health in any prioritised topic, hopefully leading to additional benefits beyond those gained from tobacco abstinence. We assume that training the GPs’ communication skills and incorporating elements of shared decision-making and motivational interviewing into the counselling process will lead to higher overall health benefits for smokers. Importantly, this broader perspective of health behaviour changes should not be paid for in lower smoking cessation rates in comparison with patients exposed to an intervention tailored to smoking cessation alone.

### Study hypothesis

We hypothesise that multidimensional and patients’ motivation-driven brief interventions by GPs improve several relevant health outcomes of smokers. We assume that these improvements surpass the beneficial effects of monothematic state-of-the-art smoking cessation counselling, and we further assume that the smoking cessation rates achievable through the novel interventions are not inferior to those known from state-of-the-art smoking cessation counselling.

To verify these hypotheses, we plan to train the GPs in the intervention group in how to coach smokers according to the Health Coaching programme [6], while the control group GPs will undergo training in monothematic smoking cessation counselling [5].

## Methods/design

### Study design and setting

A cluster randomised controlled trial (randomisation on the GP level) will be conducted with 60 German-speaking GPs from the northern part of Switzerland (see Fig. 1 for the study flow chart). The design and methodology of the study are partly based on experiences gained from a previous trial carried out by the last author in eastern Switzerland [8]. The SPIRIT checklist for this protocol can be found in Additional file 1.

**Fig. 1 Fig1:**
[figure not shown]
Study flow chart. Small coloured rectangles represent log files and case report forms used to collect data by the study centre (SC) and from general practitioners (GP) and patients (P). MPA medical assistant (medizinische Praxisassistentin)

### Eligibility and recruitment of general practitioners

All interested GPs working in outpatient primary care in the German-speaking part of Switzerland are eligible to take part in the planned study, irrespective of their contract status, their experience in primary care, their age, sex or other specifics or affiliations. Included GPs must not have had any previous training in the Health Coaching programme.

In a first step, all members of an interested network of GPs will be invited through a formal letter from the Institute of Primary Care of the University of Zurich. In case of insufficient response, email remainders will be sent out before other doctors’ networks will be included in the recruitment process, and addresses of potential participants from existing in-house and freely accessible federal databases of primary care providers will be considered.

### Cluster randomisation

Participating GPs will be listed chronologically, and GP characteristics collected prior to their allocation to either intervention or control arm. Until their required number is reached (according to the sample size calculation), the GPs will be allocated to the two equally sized study arms in blocks of 14–20 GPs each, by means of a tailored covariate constrained randomisation procedure [9] with an additional constraining criterion regarding potential contamination. In some more detail, a set of sufficiently balanced allocations with regard to the GPs' sex, contract status and practice type will be constructed and then purged from contamination-prone allocations (i.e. from those which put GPs belonging to the same group practice into different study arms), before randomly drawing the final allocation to be used in the study. All GPs from the same group practice will be allocated within the same block.

The block size was chosen to meet recommendations by Carter and Hood [10] and also with a view to training group sizes that can well be handled within the study centre’s resources. To generate the set of balanced allocations, we will use the web-based Shiny Balancer [11], and the additional reduction step will be carried out manually using Excel’s sorting and filtering capabilities. The final random draw will be carried out by a study nurse not involved in the later data analysis.

### Patient recruitment and allocation

All GPs will be asked to approach, consecutively and regardless of the reason for the consultation, current cigarette smokers at least 18 years old. By insisting on consecutive targeting of *all* smokers, we aim to eliminate selection bias very likely to arise if GPs were allowed to select patients whom they deem suitable. In order to include a total of 200 patients, each of the 60 GPs is expected to recruit three to four patients on average.

Patient inclusion criteria:Current cigarette smoker.Male or female over 18 years of age.Registered as patient in the recruiting GP’s patient base.Capable of judgement with regard to participation in the study.Signed informed consent after being informed.

Patient exclusion criteria:Severe general or psychiatric illness (e.g. malignancy, major depressive episode, dementia, etc.).Inability of the participant to follow the procedures of the study due to other reasons (e.g. language problems).Foreseeable change of general practitioner within 1 year (e.g. due to planned relocation).

Any participating patient will be assigned to the trial arm of his GP without involving further randomisation, and subsequently a set of baseline characteristics (biological and social traits and particulars of their smoking habits) will be collected from every patient included. Since not all GPs might recruit the exact same number of patients and due to the deterministic allocation of patients, we expect to record—and document—some inevitable imbalance between the trial arms with regard to patient numbers and (patient) baseline characteristics. On the other hand, randomness in the GPs' appointment schedules together with consecutive patient inclusion and coupled with the patients’ blinding with regard to the intervention (see next subsection) will translate into largely randomly composed study clusters. This will prevent extremely imbalanced trial arms.

### Blinding

Considering the nature of the interventions, full blinding of GPs and their patients in the strictest sense is not possible. However, in order to achieve the highest possible degree of double-blinding, both GPs and patients will merely be informed that the intervention is aimed at promoting beneficial health-related behaviour changes among smokers, but neither GPs nor patients will be told which of the two interventions (study or control) they provide or receive. Before consenting to participate, the patients will not be offered detailed information about the intervention they will receive, nor will they know details about the intervention in the respective other trial arm during the ongoing study. For those GPs or patients familiar with clinical studies, a minimum amount of related information will be available from registry databases and from the published protocol, which we consider inevitable.

At the end of the study, GPs will be debriefed and those in the control arm will be offered training in Health Coaching too. Ethical approval has been granted for the blinding procedures.

### Intervention

Both the study and the control intervention consist of a communication training session for the participating GPs, identical in duration and organisation but different in content. Training sessions will take 4 h and involve standardised patients (i.e. actors posing as patients) and case vignettes tailored to health-related behaviour counselling [12]. The 60 GPs will be split into groups of 7–10, and each group will then be trained within a short interval of time.

The 30 control group GPs will receive training in smoking cessation counselling as put forward by Frei von Tabak [5].

The training of the 30 GPs in the study arm will cover the key elements of the Health Coaching programme, namely patient-centred counselling, shared decision-making, motivational interviewing and the use of validated tools from existing health promotion programmes such as PAPRICA—Physical Activity Promotion in Primary Care [13], Brief Interventions in Patients with Risky Alcohol Consumption [14] and aTavola (a short intervention programme for healthy eating) [15]. Like their counterparts in the control group, the GPs in the intervention group will also be trained in smoking cessation counselling according to Frei von Tabak [5].

The intervention on the patient level will consist of either activating and coaching patients in achieving a beneficial change of their self-selected unhealthy behaviour (study intervention group) or of smoking cessation counselling (control group) in up to three (or occasionally, if necessary, more) sessions. The number of sessions will depend on progress and the needs of the patients and will be decided on by both patients and their physicians. Coaching or counselling sessions can be carried out by medical assistants or nurses provided that they take part in a training course as already described.

### Outcome measures

#### Primary outcome

The primary outcome is the difference between intervention and control group in the proportion of patients with *any relevant health-promoting change* (as defined in Table 1) in either smoking behaviour, body weight, physical activity, alcohol consumption, stress level, eating habits or another self-chosen health-related behavioural dimension. The primary outcome will be collected (including confirmatory cotinine testing) 12 months after baseline, and also as secondary outcomes at 1 and 6 months.

**Table 1 Tab1:** Definitions of health-relevant behavioural changes

Behaviour dimension: relevance criterion	Measuring method	References
Smoking: abstinence or reduction of daily number of cigarettes by ≥ 50% from a baseline of ≥ 15 cigarettes	Self-declaration, confirmatory saliva cotinine test at 12 months for quitters	[﻿18﻿, 27]
Body weight: reduction by ≥ 5% if baseline-BMI ≥ 25 kg/m^2^	Standardised home measurements	[28–30, 45, 46]
Physical activity: increase of MVPA by ≥ 90 min per week or increase of LIPA by ≥ 200 min per week, compared to baseline	Recollection-based self-declaration in questionnaire	[31–33]
Alcohol: reduction in number of standard drinks (10 g) per week by ≥ 7 drinks from a baseline of ≥ 14 drinks/week	Recollection-based self-declaration in questionnaire	[35, 36, 47]
Stress: reduction in score of the Perceived Stress Scale (PSS-10, German version) by ≥ 5, compared to baseline	Recollection-based self-declaration in validated questionnaire	[38–41]
Diet: increase by ≥ 10 in score of adapted MedDietScore questionnaire, compared to baseline	Recollection-based self-declaration in validated questionnaire	[44, 48]
Participant’s choice: increase by ≥ 2 levels on a 5 level Likert-type scale (−/0/+/++/+++)	Self-declaration in questionnaire	–

*BMI* body mass index, *LIPA* light-intensity physical activity, *MVPA* moderate- to vigorous-intensity physical activity

The chosen criteria each reflect the lowest level (cut-off point) of a behavioural change with a proven health benefit. For rationales behind the choice of these levels and a justification for choosing “any change” as the binary primary outcome, see the Discussion section.

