### Follow up

At 1, 6 and 12 months post baseline the patients will report in mail form about their health behaviour status (regarding smoking, weight, activity, alcohol, diet, stress and—if applicable—self-chosen behaviour dimension). Patients claiming to have achieved tobacco abstinence at 12 months after baseline will also be asked to provide a saliva sample for confirmatory cotinine testing.

In addition to a base compensation, the GPs will be rewarded with financial compensation for every patient providing full follow-up data.

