## Discussion

### Justification of the binary primary outcome

#### Any change

To our knowledge, the suggested composite outcome has not been used or validated before. It is largely unknown how—in terms of health benefits—a change in some behaviour dimension A compares with a change in another dimension B, and we know of no standardisation procedure to make sizes of changes comparable over different dimensions. To make matters worse, different behaviour changes are measured on different scales, and health benefits have been associated with absolute changes in some measures but with relative changes in others. We believe that, given these imponderabilities, the binary outcome “any relevant change in any component dimension” keeps the utmost possible intrinsic validity, since, firstly, the validity of the individual relevance criteria has been demonstrated and, secondly, no further assumptions on interaction or comparability of different behaviour changes are needed. Moreover, while using a dichotomous primary outcome measure inevitably incurs some loss of information, the study findings will be all the more meaningful for clinical care, provided that a statistical difference will be found [24]. The loss of information will be compensated for by analysing secondary outcomes.

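### The protocol does not settle whether control patients can score the self-chosen seventh component of the primary composite, and that component has no cited validation

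*Protocol article*

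**What the plan says.** Under Primary outcome, success is a relevant change in any of smoking, weight, physical activity, "alcohol consumption, stress level, eating habits or another self-chosen health-related behavioural dimension". Table 1 scores the last of these, labelled as the participant's choice, by self-declaration: a rise of at least two "levels on a 5 level Likert-type scale". Its reference column holds a dash, whereas the other six rows cite sources.

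The text under the table states: "The chosen criteria each reflect the lowest level (cut-off point) of a behavioural change with a proven health benefit". The Discussion (Any change) defends the composite partly on the ground that "the validity of the individual relevance criteria has been demonstrated".

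The Intervention section describes the patient-level intervention as coaching towards "achieving a beneficial change of their self-selected unhealthy behaviour (study intervention group) or of smoking cessation counselling (control group"). The Follow up section lists what patients report at 1, 6 and 12 months and attaches a condition to one item only: "stress and—if applicable—self-chosen behaviour dimension".

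Two other places point the other way. The Discussion paragraph on physical activity, which refers to all 200 participants, says in passing that participants have to document their behaviour in all seven dimensions. Strengths and limitations likewise speaks of having to collect data on seven dimensions.

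**The concern.** A composite of the any-of-seven kind is fair between arms only if each component is open to, and measured in, both arms in the same way. Six components plainly are. For the seventh, a patient needs a named dimension, a baseline rating and a later rating of that same dimension. Naming a topic is a described step of the study intervention and is not described for controls, and the follow-up item is conditional. If the item is in practice completed mainly in the intervention arm, that arm has an additional route to success that depends on data collection rather than on behaviour.

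The item is also the most subjective of the seven. Its content is defined by the patient, it is rated by the patient, and no source supports its cut-off. At stake is a superiority claim that could arise without any difference on the six referenced behaviours.

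**Working it through.** **1. Passages side by side**

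- *Who names a topic?* Intervention: the patient selects the behaviour, and coaching follows it. Control: counselling on smoking cessation, with no topic choice described. Table 3 lists the participant's choice of dimension as a covariate supplied by the GP, and these covariates are collected where applicable. That suggests the choice is recorded within counselling.
- *Who reports it?* Follow up: conditional. Physical activity and Strengths and limitations: seven dimensions, without a condition.
- *When is the baseline level fixed?* A two-level rise needs one. No section says when or how a control patient would name and rate a dimension.
- *Is it validated?* The Discussion gives rationales for the six other criteria and none for the seventh. The two general claims quoted above therefore cannot hold for it. This contradiction needs no inference.

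**2. The plan's own sample size**

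Inputs from Sample size calculations: 40% v 15%, two-sided α 5%, power 90%, patient dropout 25%, ICC 0.04, four patients per GP.

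- Unpooled normal formula: (1.960 + 1.282)² × (0.40×0.60 + 0.15×0.85) / 0.25² = 61.8, so 62 per arm. This reproduces the stated figure. (The pooled formula gives 65.)
- 2×62/0.75 = 165.3, stated as 166. 166×1.12 = 185.9, stated as 186.

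The arithmetic is not at fault. The 40% is based on subjective improvement in the self-chosen dimension in the preceding study. The 15% is 10% cessation plus 5% on other dimensions.

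**3. What unequal access to the seventh item would do**

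Effective patients per arm with 200 recruited: 200 × 0.75 / 1.12 / 2 = 67.0.

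Assumptions, not in the documents: success on the six shared components p = 15% in both arms; a share q choosing an off-list topic; a share s = 0.5 of those improving, independently of the six; controls scoring the item at a fraction f of the intervention rate.

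- Intervention rate = p + (1−p)·q·s
- Control rate = p + (1−p)·q·s·f

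For q = 10%: 0.15 + 0.85×0.05 = 19.3%. For q = 20%: 0.15 + 0.85×0.10 = 23.5%. For q = 30%: 0.15 + 0.85×0.15 = 27.8%.

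Exact probability that the two-sided 5% chi-square test rejects, n = 67 per arm:

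| q | controls never score it (f=0) | half as often (f=0.5) | alike (f=1) |
|---|---|---|---|
| 10% | 9.8% | 6% | 5% |
| 20% | 23.6% | 9% | 5% |
| 30% | 43.9% | 14% | 5% |

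Without the item the test rejects 4.8% of the time.

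Other settings with f = 0:

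- shared rate 25% instead of 15%: 7.7%, 15.9%, 29.4% for q = 10%, 20%, 30%;
- s = 0.25 instead of 0.5: 6%, 10%, 16%;
- q = 5% with s = 0.5: 6%.

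**4. What dropping the item from the primary outcome would cost**

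If the planned 40% includes the item, and a share u of patients who fail on the other six succeed on it alone, the six-component rate is 1 − 0.60/(1−u). Power and n use the pooled formula, which gives 88.6% power at 40% v 15% with 62 per arm.

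| u | six-component rate | power at 62 per arm | n per arm for 90% |
|---|---|---|---|
| 5% | 36.8% | 80% | 83 |
| 10% | 33.3% | 67% | 113 |
| 15% | 29.4% | 49% | 173 |

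**The case against.** A reader might infer that the seventh component exists only in the intervention arm, so that the composite is biased by construction. The documents do not say so. Follow up speaks of the patients without splitting them by arm, and the condition may cover any patient in either arm who names a further dimension. The Intervention section describes what is counselled, not what the questionnaire asks. The remarks on seven dimensions cut directly against exclusion of controls. This objection stands: exclusion is an inference, and the most the text supports is an inconsistency.

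It can also be said that more improvement on a chosen topic is the effect the trial seeks, so equality on six components is not its null hypothesis. That stands where the item is collected alike in both arms. It does not cover a difference that arises because one arm is asked and the other is not, and the current text cannot separate the two.

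The illustration depends on choice shares that no document gives. Its one-half improvement rate is borrowed from declared improvement in any self-chosen dimension, not from a two-level rise on an off-list topic. That stands too, and it is why the table runs down to no inflation.

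Finally, the article admits recall and desirability bias, says the composite has not been validated before, and does not tell patients which intervention they receive. These are mitigating, but they do not address unequal collection, and they sit beside a claim that each criterion is validated.

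**Conclusion.** Two things are established from the text alone. The seventh criterion has no reference or rationale, which contradicts the general claims of proven benefit and demonstrated validity. And the article is inconsistent on whether every patient, controls included, documents it.

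The bias is conditional on how that inconsistency resolves. If controls cannot score the item, or have less opportunity to, the comparison shifts towards the intervention; if both arms complete it alike, the test keeps its level. With 15% on the shared components, 10–20% choosing off-list and half improving, rejection is 10–24%, 6–9% or 5% depending on control access. The direction is firm under unequal access; the size rests on assumed shares.

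The stronger conclusion, that the item must leave the primary outcome, does not follow. Removal is a trade-off, because the 40% planning rate rests on self-chosen improvement and power would fall.

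**What to change.** 1. Reconcile Follow up with the seven-dimension statements under Physical activity and Strengths and limitations. Have every patient in both arms name and rate a self-chosen dimension at baseline, before any counselling, and rate that same dimension at each follow-up.
2. Prespecify the composite of the six referenced dimensions as a key sensitivity analysis, report the seventh item separately by arm, and make a superiority conclusion depend on whether the six-component result agrees.
3. Reword the statement under Table 1 and the one in the Discussion so that neither covers the seventh criterion.

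The cost is one extra baseline item and one extra analysis. The Timeframe section says patient inclusion had begun in late 2018. Patients already counselled without a baseline rating cannot be given one afterwards, so their number by arm should be reported, and for them the six-component analysis is the safeguard.

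Moving the primary outcome itself to six components is an option. It lowers the expected intervention rate, so the 40% assumption and the stated power would have to be restated.

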#### Physical activity

Current guidelines recommend a minimum of 150 min of physical activity per week of at least moderate intensity (corresponding to ≥ 7.5 MET∙h). Beneficial health effects have been satisfactorily demonstrated for roughly 60% of this amount, for example by Wen et al. [31]. See also the recommendations of the US Physical Activity Guidelines Advisory Committee [32]. According to both sources, additional health effects have been shown for further activity increases by the same amount. Equivalent amounts or equivalent *additional* amounts of physical activity can be achieved with similarly beneficial results at lower intensities but with longer duration [33].

The obvious and tempting idea of using tracking devices had to be discarded on the grounds of practicability (distribution and maintenance of the devices), methodological considerations (recording of baseline activity before the first coaching or counselling session) and due to the sheer costs of providing appropriate sensors to all 200 participants. Out of consideration for the participants (who need to document their health behaviour in all seven dimensions) we also decided against relying on diaries to capture the amount of physical activity. This decision is backed by Timperio et al. [34], who point out that the use of physical activity logbooks does not increase estimates of validity of 7-day recall physical activity questionnaires.

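### The light-activity limb of the physical activity criterion ignores a fall in moderate activity, so swapping or relabelling the same minutes counts as a primary-outcome success

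*Protocol article*

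**What the plan says.** In Table 1 (Outcome measures, Primary outcome) the physical activity criterion is "increase of MVPA by ≥ 90 min per week or increase of LIPA by ≥ 200 min per week", each measured against baseline. The measuring method is "Recollection-based self-declaration in questionnaire". Below the table the article states: "The chosen criteria each reflect the lowest level (cut-off point) of a behavioural change with a proven health benefit".

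The primary outcome is "any relevant change in any component dimension" (Discussion, Any change), so meeting either limb of this one criterion makes the patient a success.

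The thresholds are explained in the Discussion under Physical activity. The guideline amount is 150 min/week at moderate intensity or above, which the article equates with 7.5 MET·h. It then says: "Beneficial health effects have been satisfactorily demonstrated for roughly 60% of this amount". For the light-intensity limb it argues that equivalent amounts, or equivalent additional amounts, "can be achieved with similarly beneficial results at lower intensities but with longer duration". Nowhere does the article say how a gain in one band is scored when the other band falls.

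**The concern.** The argument for the LIPA limb is one of equivalence: enough extra light activity is worth as much as 90 extra minutes of moderate activity. That holds only if the light activity comes on top of what the patient already did. The scoring rule does not test this, because it looks at the change in LIPA alone.

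Two kinds of patient then succeed without any gain. One has really moved from moderate to light activity. The other has not changed, but recalls the same activity as moderate on the first questionnaire and light on the last. Either becomes a success on the whole composite unless already a success on another dimension. If this happens equally in both arms, it pulls the two success rates together. Intervention-arm GPs, but not control GPs, are trained with a physical activity promotion tool (Intervention section), so equal frequency is not assured.

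**Working it through.** **1. The plan's own threshold.** Inputs from Discussion, Physical activity: 150 min = 7.5 MET·h, benefit at about 60%.

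- 0.60 × 150 = 90 min, which reproduces the MVPA threshold.
- 7.5 MET·h / 2.5 h = 3 MET, so 90 min = 1.5 h × 3 = 4.5 MET·h.
- If 200 min LIPA is equivalent, LIPA is implicitly valued at 4.5 / (200/60) = 1.35 MET.

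The two thresholds therefore imply an exchange rate of 90 min MVPA for 200 min LIPA. A net index on that scale is

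I = change in MVPA/90 + change in LIPA/200,

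where I = 1 is one threshold's worth of additional activity.

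**2. The Table 1 rule applied to example changes (min/week).**

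| Change in MVPA | Change in LIPA | Table 1 | Total minutes | I |
|---|---|---|---|---|
| 0 | +200 | success | +200 | 0 + 1 = 1.00 |
| −90 | +200 | success | +110 | −1 + 1 = 0.00 |
| −200 | +200 | success | 0 | −2.22 + 1 = −1.22 |
| −210 | +200 | success | −10 | −2.33 + 1 = −1.33 |

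The third row is the clear case: no extra minutes and lower intensity, or no change at all if it is relabelling. Its net energy is 200 × (M − 3)/60 MET·h, where M is the MET value of LIPA. That is −5.5 at the implied 1.35, −3.3 at an assumed 2, and −1.7 at an assumed 2.5. It is negative for any M below 3, so this case does not depend on the choice of M. The second row does: on the implied exchange rate the gain is exactly cancelled, but at an assumed 2 MET it is −4.5 + 6.7 = +2.2 MET·h.

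**3. What dilution would cost, as illustration only.** Inputs from Sample size calculations: 40% against 15%, two-sided α 5%, power 90%.

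- n per arm = (1.960 + 1.282)² × (0.40 × 0.60 + 0.15 × 0.85) / 0.25² = 61.8, so 62, which reproduces the plan's figure.
- Let q be the probability, assumed equal in both arms, that a patient who would otherwise fail becomes a success only through an offset LIPA gain. Each rate p becomes p + (1 − p)q, and the difference becomes 0.25 × (1 − q).

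| q (assumed) | Rates | Power at 62 per arm | n per arm for 90% |
|---|---|---|---|
| 0 | 40.0% vs 15.0% | 90% | 62 |
| 2% | 41.2% vs 16.7% | 88% | 67 |
| 5% | 43.0% vs 19.3% | 84% | 75 |
| 10% | 46.0% vs 23.5% | 77% | 89 |

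Nothing in the documents fixes q.

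**The case against.** Several points on the other side are fair.

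- **Frequency.** The article gives no standard deviation of change in either band and no correlation between them. The −200/+200 case needs a smoker who reports at least 200 min/week of MVPA at baseline, above the 150 min guideline. Relabelling counts only if at least 200 min/week moves from moderate to light. The questionnaire is not shown and may define the bands well enough to limit this. All of this stands: no share of spurious successes can be claimed.
- **Recall noise.** Most false successes on this dimension may come simply from noisy recall crossing a threshold. Strengths and limitations already concedes recall, desirability and interpretation bias. That stands too, but it does not cover a rule that accepts an offset gain even when activity is measured perfectly.
- **Other outcomes.** Weekly activity time is a secondary outcome (Table 2), and the underlying changes will be compared between arms (Statistical analysis). This may reveal the problem but does not alter the composite.
- **Weighing changes.** The article declines to weigh one dimension against another for want of a common scale. Within physical activity it has one, because it sets two thresholds on an equivalence argument.

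A reader might infer that the MVPA limb is equally faulty, since +90 MVPA with −90 LIPA is a success at zero extra minutes. The documents do not support treating it the same way. Their case for the MVPA limb is made in time at moderate intensity or above, with no condition on LIPA, so a real shift of 90 min from light to moderate is the kind of change it means to count. A net condition there would reject that shift (I = 1 − 0.45 = 0.55). It would still pass light-to-moderate relabelling of 164 min or more, since 1/(1/90 − 1/200) = 163.6.

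A reader might also infer that total activity falls in every such case. It does not. With MVPA −180 and LIPA +200, total minutes rise by 20, and energy falls (9.0 MET·h lost) only if LIPA is below 9.0/(200/60) = 2.7 MET, a value the documents do not give.

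**Conclusion.** The point holds for the LIPA limb. As written, Table 1 counts a patient with MVPA −200 and LIPA +200 min/week as a primary-outcome success although no additional activity was gained. This is at odds with the article's rationale and with its claim of proven benefit for each criterion. It follows from the wording alone and needs no assumption beyond light activity being less intense than moderate.

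Its effect on the trial result cannot be derived from the documents. If such cases are equally frequent in both arms they dilute the difference: a net 2% to 10% of otherwise failing patients would take power from 90% to between 88% and 77%, but those percentages are assumed. If the frequency differs by arm, the comparison is biased in a direction the documents do not reveal. The fault concerns one limb of one of seven dimensions, so it is worth correcting but does not undermine the design. The sample size calculation itself is not in question here.

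**What to change.** Keep the MVPA limb as it is. Count the LIPA limb only if LIPA has risen by at least 200 min/week **and** change in MVPA/90 + change in LIPA/200 is at least 1. The added condition bites only when MVPA has fallen. A pure +200 min LIPA still qualifies (I = 1), and a larger LIPA gain can absorb some loss of MVPA: −90 with +400 gives −1 + 2 = 1. The −200/+200 swap and the matching relabelling no longer count. The rate comes from the article's own two thresholds, so no outside MET value is needed. The rule should be fixed before outcomes are seen by arm.

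The cost is small. Table 1 already requires minutes in both bands at baseline and follow-up, so this is a scoring change with no new items. The success rate on this dimension may be slightly lower, and a patient just at the LIPA threshold with a small fall in MVPA fails (+200 with −10 gives 1 − 0.11 = 0.89). Relabelling from light to moderate cannot be told from true intensification on self-report and should be named as a limitation.
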